### Recruitments and randomization

This study will be conducted in the outpatient ENT department of the Eye and ENT Hospital of Fudan University in Shanghai, China. Our institution is a specialized hospital focused on otorhinolaryngology. In addition, we developed an app—the Fudan Tinnitus Relieving System (FTRS)—that will be used for the management, treatment, data collection, and efficacy analysis of tinnitus patients. The participants will be primarily included in the study after being diagnosed with probable chronic subjective tinnitus with bothersome symptoms after the screening procedure. Screening for hearing and tinnitus testing typically consists of PTA, speech audiometry test, and distortion product otoacoustic emissions (DPOAE) along with several widely accepted tinnitus questionnaires such as the THI for tinnitus severity, the visual analog scale (VAS) for tinnitus loudness, and the HADS and AIS-8 for mental health status. The entire test will generally take a mean time of approximately 30 min. Participants will scan the two-dimensional code we supply via their smartphones and will fill out the questionnaires online through the FTRS.

Interested patients will be directed to the research room to receive the necessary details of the study. Before participation, informed and written consent will be obtained from all participants by the principal investigator. The randomization will be stratified by the THI score (≤ 36 or > 36 [18]) based on the baseline assessment in order to avoid an uneven distribution of patients. An independent researcher who is not involved in the recruitment process or outcome measurement will generate a random sequence (http://www.random.org) to randomly assign the participants in a 1:1 allocation to treatment using HAs or to the WLC group. The randomization sequence will be concealed in sequentially numbered sealed and opaque envelopes. Participants will then be notified via telephone or email which group they are allocated to by the staff member who kept the randomization sequence file and who will not participate in any subsequent assessment of the patients. Data analysts, study coordinators, and outcome assessors will remain unaware of the group assignments until the primary analyses are completed.

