##### PTA

PTA calculates the average hearing thresholds in decibels (dB) obtained at multiple frequencies. The test is administered in a double-walled soundproof audiometric treatment room with a speaker located 1 m directly in front of the participant. An average hearing threshold above 25 dB at high frequencies (2–8 kHz) is defined as high-frequency SNHL. Participants will be required to undergo PTA at 0.5, 1, 2, and 4 kHz to derive accurate hearing threshold data.

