### Time points

All of the enrolled patients will undergo a clinical evaluation, sign the consent, and record their basic personal information at the baseline measurement. After the stratified randomization, patients will be informed of their group allocation and will correspondingly receive the intervention over the next 6 months. The follow-up visits will be at 3 months after baseline measurement (*t*_1_, mid-way through the intervention) and at 6 months (*t*_2_, the end of the study). The follow-up assessments will comprise the THI, PTA, SRS, DPOAE, VAS, HADS, and AIS-8, and related questionnaires will be developed and distributed in the FTRS. The schedule of enrollment, interventions, and assessments adhering to the SPIRIT 2013 statement is outlined in Fig. 2.

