In addition, a large population of tinnitus patients who suffer from related psychological distress seems to have negative emotional performance [44]. So far, there has been little agreement on how best to manage the mental status of tinnitus patients. The most widely recognized strategy focusing on neuropsychiatric complications is CBT. However, to date, research has not determined whether CBT improves tinnitus’s perceptual characteristics or improves the general quality of life by changing the awareness of tinnitus [41]. Moreover, CBT is ineffective for patients with combined SNHL. Another potential problem with CBT is that it is a time and energy-consuming therapy and requires substantial support from psychiatrists, psychologists, and family connections. HAs, in contrast, are simple, safe, and easy to use, and prior studies have noted the importance of HA use in mental status management in tinnitus patients [14, 42]. To the best of our knowledge, there is no evidence supporting a link between HA treatment and the preservation of residual hearing, and more detailed RCT studies are still required to compensate for the shortcomings of previous studies [16], as well as to further determine the efficacy of HAs in patients suffering from tinnitus with coexisting SNHL.

The present study, which differs from other trials, seeks to comprehensively prove that HAs are effective in patients with tinnitus and hearing impairment and to further explore the residual hearing protection by HA treatment in the intervention group. The strengths of the study rest on several aspects. For instance, we designed the HA treatment as a stand-alone intervention with clearly defined inclusion criteria, including the subjective tinnitus duration and specific PTA thresholds per frequency. Thus, it will be possible to avoid combining the study with other tinnitus treatments and avoid selection bias, which will improve the reliability and credibility of the observation results. Additionally, patients will be recruited from an ENT-specialized hospital, where adequate eligible participants can be obtained. Moreover, the study findings might contribute to profound advances in tinnitus treatments and may serve as a helpful reference for other countries. When the efficacy of the HA can be verified, it may have positive implications in the clinical setting as to its role in alleviating tinnitus and preventing the coexisting SNHL from deteriorating.

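### The only prescribed audiometry frequencies stop at 4 kHz, while entry and the definition of high-frequency hearing loss rest on a 2–8 kHz average

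*Protocol article*

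**What the plan says.** The Participants section of the protocol article admits patients with mild high-frequency SNHL, meaning a pure-tone audiometry (PTA) average of 25–40 dB over 2–8 kHz. The PTA subsection, under Secondary outcome measures, gives the matching definition: "An average hearing threshold above 25 dB at high frequencies (2–8 kHz) is defined as high-frequency SNHL". Its next sentence sets the test: "Participants will be required to undergo PTA at 0.5, 1, 2, and 4 kHz to derive accurate hearing threshold data". No other list of test frequencies appears in the article.

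PTA is named in two other places, both without frequencies. Under Recruitments and randomization: "Screening for hearing and tinnitus testing typically consists of PTA, speech audiometry test, and distortion product otoacoustic emissions (DPOAE". Under Time points, for the 3- and 6-month visits: "The follow-up assessments will comprise the THI, PTA, SRS, DPOAE, VAS, HADS, and AIS-8".

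The Discussion counts as a strength "clearly defined inclusion criteria, including the subjective tinnitus duration and specific PTA thresholds per frequency". It also hopes to show that hearing aids can stop the accompanying SNHL from getting worse.

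**The concern.** The band that decides who has the condition runs to 8 kHz, and the prescribed test ends at 4 kHz. Two adjacent sentences of one subsection therefore do not fit together, and the second does not fit the entry criterion either.

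What is at stake depends on which test the list governs.

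- **Screening.** If the list applies at entry, the criterion has to be judged from an incomplete set of thresholds. The enrolled group may then differ from the mild high-frequency group that the conclusions will name.
- **Outcome visits only.** If the list applies only at follow-up, the upper part of the qualifying band is not remeasured, although preservation of residual hearing is in the trial's title.

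**Working it through.** The protocol gives no figure to reproduce here. The check compares frequency sets and then does arithmetic on assumed audiograms.

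**Step 1: frequency sets.**

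| Place in protocol | Frequencies |
|---|---|
| Participants (entry) | average over 2–8 kHz |
| PTA (definition of SNHL) | average over 2–8 kHz |
| PTA (test list) | 0.5, 1, 2, 4 kHz |
| Recruitments and randomization (screening) | none named |
| Time points (3 and 6 months) | none named |

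Of the four listed frequencies, only 2 and 4 kHz lie in the qualifying band. No section prescribes a threshold above 4 kHz.

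**Step 2: size of the gap, if the list governs screening.** Two assumptions are needed, and the protocol states neither. The band average is taken as the mean of 2, 4 and 8 kHz, and staff with only the listed frequencies are taken to average 2 and 4 kHz. Write T2, T4 and T8 for the thresholds.

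- M24 = (T2 + T4)/2
- M248 = (T2 + T4 + T8)/3 = (2·M24 + T8)/3
- M248 − M24 = (T8 − M24)/3

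If 8 kHz is 15, 30 or 45 dB worse than M24, the two averages differ by 5, 10 or 15 dB. The entry window is 40 − 25 = 15 dB wide, so the gap is 33%, 67% or 100% of it.

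**Step 3: examples (assumed audiograms).**

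| 2/4/8 kHz (dB) | M24 | M248 | In 25–40 on M24? | In 25–40 on M248? |
|---|---|---|---|---|
| 30/40/65 | 70/2 = 35.0 | 135/3 = 45.0 | yes | no |
| 15/25/45 | 40/2 = 20.0 | 85/3 = 28.3 | no | yes |
| 25/35/45 | 60/2 = 30.0 | 105/3 = 35.0 | yes | yes |

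The first patient would be wrongly admitted and the second wrongly refused. The third is classified correctly either way, so the error is possible but not inevitable.

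**Step 4: what the missing threshold decides.** From 25 ≤ (2·M24 + T8)/3 ≤ 40, a patient qualifies only if 75 − 2·M24 ≤ T8 ≤ 120 − 2·M24. With M24 = 30 dB, T8 must lie between 15 and 60 dB. With M24 = 35 dB, it must lie between 5 and 50 dB. The listed frequencies do not supply T8.

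**Step 5: the other reading.** Suppose screening uses a fuller audiogram and the list governs only the 3- and 6-month tests. Eligibility is then sound, but M248 can be computed at entry and not afterwards. Change can be followed at 2 and 4 kHz only. For the part of the band above 4 kHz there is no threshold after baseline in either arm.

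**The case against.** The strongest reply is that the list stands in an outcome section. Entry is set under Participants, and screening is described separately without frequencies. Staff told to find a 2–8 kHz average would have to test that band. The source is also a condensed journal article, so the screening audiogram may be fully specified elsewhere. Much of this stands. A reader might infer that eligibility cannot be determined, or that 8 kHz is never measured. The article does not support either, because nothing in it limits screening audiometry to 0.5–4 kHz. The substitution of a 2/4 kHz average is likewise my assumption, not the protocol's instruction.

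The reply does not remove the conflict. The frequencies are not left out of the article. They are stated, directly after a definition that they cannot serve. The outcome-only reading moves the problem to follow-up.

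Two further defences deserve an answer.

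- **Low-frequency aim.** The Discussion stresses protecting low-frequency residual hearing, which explains why 0.5 and 1 kHz are tested. It does not explain why the band above 4 kHz is left out, given the hope of halting a loss defined on 2–8 kHz.
- **Otoacoustic emissions.** These are repeated at follow-up, and the protocol credits them with specificity at high frequencies. They are presented as a test of outer hair cells, whereas SNHL is defined by hearing thresholds, so they do not replace the missing value.

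A reader might also infer bias in the treatment comparison. That does not follow. Eligibility is settled before 1:1 randomization, so entry errors do not depend on the arm, and the primary outcome is the Tinnitus Handicap Inventory, not hearing.

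**Conclusion.** The conflict holds on the text alone: the prescribed frequencies cannot yield the average on which both entry and the definition of SNHL rest. Its consequence takes one of two forms. If the list governs screening, patients can be misclassified in both directions, by 5 to 15 dB on a 15 dB window when 8 kHz is 15 to 45 dB worse than the 2/4 kHz mean. That affects which population the results describe. If the list governs only the outcome visits, the trial cannot show whether SNHL as it defines it was preserved.

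The decibel figures rest on assumed audiograms and on reading the band as 2, 4 and 8 kHz. I give no share of patients misclassified, because the protocol offers no distribution of thresholds from which to estimate one, and the share would be zero if screening covers the full band. Severity is moderate: the primary comparison is not threatened, but either the description of the population or a headline secondary aim is.

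**What to change.** Reconcile the Participants, Recruitments and randomization, and PTA sections:

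1. Extend the PTA list to 0.5, 1, 2, 4 and 8 kHz, with 6 kHz if the band is meant to include it. Keep 0.5 and 1 kHz for low-frequency residual hearing.
2. State that the same list applies at screening, 3 months and 6 months.
3. State that the 2–8 kHz average is the mean of exactly the tested frequencies in that band.

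The Trial status section plans recruitment from July 2022 to July 2023, and the article appeared in December 2022, so some patients may already have been screened. For them, record which frequencies were tested and report how many have a complete 2–8 kHz average at entry.

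The cost is one or two more frequencies in a test already performed, a minute or two per session, and a short change to the protocol text. No extra visit, staff or equipment should be needed.

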##### DPOAE

The DPOAE test might help determine the mechanism behind tinnitus because it determines whether or not the outer hair cells are overexcited or damaged [25]. DPOAE has the advantage of high-frequency specificity and is an objective and non-invasive measurement for diagnosing hearing impairments [26], which can benefit patients with tinnitus and SNHL.

##### VAS

To measure the subjective perception of tinnitus loudness, we will use the VAS, which requires the patient to mark the severity of their tinnitus on a horizontal scale from 0 to 10. It is easy to administer and widely used as a continuous scale for evaluating tinnitus from asymptomatic to unbearable. The higher the score, the more severe the symptoms.

##### HADS and AIS-8

The HADS and the AIS-8 are two questionnaires for measuring mental status. The HADS consists of 14 items equally divided into two dimensions, namely a depression subscale (HADS-D) and an anxiety subscale (HADS-A) [27, 28]. The grades are valued by scoring as negative (0–7) or positive (8–21). The HADS is easy to use, and the Chinese version’s adequate internal reliability and discriminant validity have been confirmed [29]. Sleep is integral for optimizing brain function and mental states, and the AIS comprises eight items that commonly measure difficulties in falling asleep or maintaining sleep in order to quantify the presence of insomnia [30]. The higher the AIS score, the lower the sleep quality and mental status, and the AIS identifies three types of sleep disorders—no insomnia (score below 4 points), suspicion of insomnia (4–6 points), and insomnia (7–24 points).

##### APHAB

Participants in the HA group will also be asked to complete the APHAB questionnaire in order to additionally evaluate their listening and communication skills. The APHAB consists of 24 questions scored on four six-item subscales [31]. The ease of communication, reverberation, and background noise subscales indicate the characteristics of HA amplification under various environmental conditions, revealing the level of speech comprehension, while the aversiveness to sound subscale indicates the discomfort caused by environmental noise. The subscales of the questionnaire are evaluated separately.

### Time points

All of the enrolled patients will undergo a clinical evaluation, sign the consent, and record their basic personal information at the baseline measurement. After the stratified randomization, patients will be informed of their group allocation and will correspondingly receive the intervention over the next 6 months. The follow-up visits will be at 3 months after baseline measurement (*t*_1_, mid-way through the intervention) and at 6 months (*t*_2_, the end of the study). The follow-up assessments will comprise the THI, PTA, SRS, DPOAE, VAS, HADS, and AIS-8, and related questionnaires will be developed and distributed in the FTRS. The schedule of enrollment, interventions, and assessments adhering to the SPIRIT 2013 statement is outlined in Fig. 2.

**Fig. 2 Fig2:**
[figure not shown]
Schedule of enrollment, interventions, and assessments according to the SPIRIT 2013 guidelines

### Adverse events

Adverse events (AEs) are defined as any untoward medical occurrence (such as any abnormal signs and symptoms) in participants in the research regardless of whether or not they are involved in the intervention group. Severe AEs are those leading to hospitalization, discontinuation of treatment, or fatal or life-threatening conditions. AEs will be collected and recorded during the overall trial in our study. There will be two interim analyses carried out to monitor the treatment effects, with further recruitment occurring throughout these interim analyses. One will be carried out when approximately 30 participants have been recruited, and the other will be at 3 months following recruitment. Treatment safety evaluation will be based on AE occurrence and the use of concomitant treatments. Both groups of patients will be allowed to continue their concurrent routinely indicated treatments, and the details of concomitant treatments will be monitored. However, HAs are generally well-tolerated and are not likely to elicit any risk of AEs. An experienced HA-fitting technician will manage the HA intervention if a patient complains about serious side effects.

### Participant withdrawal

The patients will be entitled to withdraw from the study after providing informed consent. We have no stopping guidelines for futility, and if a participant is removed from the study, the precise reasons for withdrawal conditions will be documented and explained. During the overall study time, online contact via a WeChat group and telephone instant messaging will be offered to all of the participants, which will be helpful in managing the trial more effectively and easily.

### Blinding

For this intervention, it is not feasible to blind participants and clinicians regarding the treatment condition owing to the nature of the clinical treatment modalities. However, by separating the intervention and analysis staff, independent investigators in our hospital will perform all follow-up evaluations blinded to the group allocation. We will also attempt to minimize assessment bias and achieve the maximum trial blinding through the following measures: (1) both the data collectors and the assessors will be trained to achieve high interrater reliability, (2) participants and data collectors will be masked as far as possible to block size when collecting the data, and (3) the outcome data assessor will be blinded from randomization until the statistical analyses of the experimental outcomes are completed.

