## Methods/design

### Study design and settings

The study protocol will follow the *2013 Standard Protocol Items: Recommendations for Interventional Trials (SPIRIT) Statement* [17] (Additional file 1). This study is a prospective, single-center, outcome assessor and data analyst-blinded, randomized, controlled trial with superiority test in the framework lasting 6 months with an allocation ratio of 1:1 for the intervention and WLC groups. Patients will be recruited from the tinnitus outpatient clinics of the Eye and ENT Hospital of Fudan University in Shanghai, and the trial will be conducted by qualified and well-trained doctors, investigators, and HA technicians using appropriate experimental facilities.

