### Outcome measurements and follow-ups

#### Primary outcome measure

The primary outcome measure is the change in the THI score [20]. The THI is a self-administered test including 25 questions that determine the degree of function, emotional status, and adverse reactions in the patient with tinnitus. The respondent answers the questions on a 3-point Likert scale with responses of “no” (0 points), “sometimes” (2 points), and “yes” (4 points) yielding an overall score ranging from 0 to 100. The following criteria are used to determine effectiveness [21]: curative = THI score decreased to less than 16 points; significantly effective = THI score decreased by more than 17 points; and ineffective = THI score decreased by less than 17 points, or even increased. The THI has been demonstrated to be a well-known, reliable, and valid clinical tool when evaluating the severity of tinnitus and for assessing the performance of HAs [22]. The proposed study will use the THI Chinese (Mandarin) version [23].

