This study is not exempt from limitations. For example, most self-report questionnaires are subjective and are prone to reporting bias due to participants’ non-adherence and vague memory. Participants have to be encouraged to answer truthfully, and to some extent, the outcomes provided by caregivers can be added as complementary information. Also, the use of WLC groups has been regarded as an ethical alternative to control groups, but this can potentially pose problems. As a solution to the limitation that participants in the WLC group are stalled at the stage of change regarding readiness, we set the enrollment to be mild and acceptable symptoms, and we will provide periodic health advice to all participants. Another point worth mentioning is that cochlear implant (CI) technology currently effectively restores hearing by stimulating the cochlear nerve [44, 45]. However, although CIs are capable of protecting residual hearing, they are invasive and are prohibitively expensive. Accordingly, early benefits from HA use can be expected in patients with residual hearing. Nevertheless, if the effectiveness is less pronounced with HAs, the use of CIs may be necessary.

To conclude, this will be the first randomized controlled trial to evaluate the efficacy of HAs on sound perception and residual hearing preservation among tinnitus patients with SNHL in China. Despite its limitations, this study is unique and will contribute to knowledge about HAs’ roles in residual hearing preservation in these patients. The results from this trial are expected to provide support for doctors to provide more effective advice in clinical practice.

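### Assessor blinding is claimed for every follow-up evaluation but cannot apply to the primary outcome, which unblinded participants rate themselves

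*Protocol article*

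**What the plan says.** The protocol article makes the blinding claim at two levels.

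- **Label.** The section on study design and settings calls this a "prospective, single-center, outcome assessor and data analyst-blinded, randomized, controlled trial". The Methods paragraph of the Abstract uses the same label.
- **Scope.** Only the Blinding section states how far the assessor blinding reaches: "independent investigators in our hospital will perform all follow-up evaluations blinded to the group allocation".

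The Blinding section also concedes that "it is not feasible to blind participants and clinicians regarding the treatment condition". The section on recruitment and randomization says participants learn their allocation by telephone or email.

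On who does the rating, the primary outcome section says: "The THI is a self-administered test including 25 questions". The recruitment section says of participants at screening that they "will fill out the questionnaires online through the FTRS", and the Time points section places the follow-up questionnaires in the same app. The VAS section has the patient mark the scale. The section on HADS and AIS-8 describes both as questionnaires.

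The limitations paragraph of the Discussion accepts that self-report is open to reporting bias. It attributes this to non-adherence and poor recall.

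**The concern.** Blinding an outcome assessor protects a result when the person who assigns the score does not know the arm. For the THI that person is the participant, who does know. No blinded investigator performs that evaluation, so the scope claimed in the Blinding section is wrong for the outcome on which the trial will be judged.

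The control is a waiting list without a sham device, and people unwilling to use hearing aids daily are excluded. Every control has therefore accepted the device in principle and knows it has been deferred. Expectation in one arm and disappointment in the other could plausibly both move subjective scores in favour of the hearing aid. Readers and evidence reviewers who take the design label at face value would apply it to the THI result and credit that result with a protection it does not have.

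**Working it through.** The article gives no figure to reproduce, so the check sets its sections side by side.

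**Step 1: who scores each measure.** The Time points section lists seven follow-up measures for all participants. APHAB is left out because only the hearing-aid arm completes it.

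| Measure | Who gives the score | Basis | Can assessor blinding apply? |
|---|---|---|---|
| THI (primary) | Participant | Explicit: primary outcome section | No |
| VAS | Participant | Explicit: VAS section | No |
| HADS | Participant | Inferred: questionnaire, completed in the app | No |
| AIS-8 | Participant | Inferred: questionnaire, completed in the app | No |
| PTA | Test staff | Staff-administered test | Yes |
| SRS | Test staff | Staff-administered test | Yes |
| DPOAE | Test staff | Staff-administered test | Yes |

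The inference for HADS and AIS-8 combines three sections: recruitment (questionnaires filled out online by participants), HADS and AIS-8 (both are questionnaires) and Time points (follow-up questionnaires distributed in the app).

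**Step 2: does the rater know the arm?** Yes for the first four rows. Participants are notified of their allocation, and the Blinding section says they cannot be blinded.

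**Step 3: do the listed safeguards reach a self-completed score?**
- Training for agreement between raters: a self-completed form has no pair of raters.
- Masking of block size: this protects the allocation sequence. It does not hide the arm a participant has already been told.
- Blinding of whoever handles the outcome data until the analyses are complete: this is real, but it acts on scores that unblinded participants have already given.

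**Step 4: count.** Assessor blinding can apply to 3 of 7 measures and cannot apply to 7 − 3 = 4, including the primary. Analyst blinding applies to 7 of 7.

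**The case against.** The strongest reply is that the article hides nothing. It says openly that participants are unblinded and that the THI is self-administered, and it lists reporting bias among its limitations. The label names assessors and analysts, never participants. An open comparison is also hard to avoid when a hearing aid is set against a waiting list. All of this stands, and it makes the fault one of description, not of concealment or of an avoidable design. It does not rescue a statement that covers every follow-up evaluation, and the limitations paragraph does not name knowledge of the arm as a cause of bias.

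A reader might infer four stronger points that the documents do not support.

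- **That no stated blinding protects the THI result.** The recruitment section keeps analysts, coordinators and assessors unaware of allocation until the primary analyses are done. Analyst blinding therefore does cover the THI.
- **That caregivers will supply THI scores.** The Discussion says only that "the outcomes provided by caregivers can be added as complementary information". No Methods section feeds caregiver data into a score or an analysis, so this does not contradict self-administration.
- **That audiological testers will be unblinded by seeing the device.** A condensed article need not describe test-room procedure, so its silence is no evidence. Requiring removal of the device would also settle whether SRS and PTA are tested aided or unaided, which is a separate question.
- **That the bias can be sized against a detectable effect.** Suppose the bias is *b* standard deviations. With 28 per arm and 80% power, the detectable difference is 2.8 × SD × √(2/28) ≈ 0.75 SD. The ratio is *b*/0.75: the SD cancels and only the assumed *b* remains, so the ratio carries no information from this trial.

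**Conclusion.** The point holds as a misstatement of blinding. The Blinding section claims blinded assessment for all follow-up evaluations, and the Abstract and design section carry a matching label. The primary outcome and three secondary outcomes are rated by participants who know their arm. For THI and VAS this is explicit. For HADS and AIS-8 it rests on the inference shown above.

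Its extent is four of the seven measures taken in both arms. The size of any reporting bias cannot be derived from the documents, and the conclusion does not depend on it. The design can stand, as can assessor blinding for PTA, SRS and DPOAE and analyst blinding throughout. What cannot stand is the unrestricted assessor-blinding claim, because it affects how much weight the THI conclusion can bear.

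**What to change.** 1. In the Abstract (Methods and design), the section on study design and settings, and the Blinding section, replace the general claim with wording such as: *Outcome assessors are blinded for PTA, SRS and DPOAE. THI, VAS, HADS and AIS-8 are participant-reported and unblinded. Data analysts are blinded for all outcomes.*
2. In the Blinding section, restrict the sentence on independent investigators to those three staff-administered tests.
3. State that the conclusion on the THI comes from an unblinded comparison with a waiting list.
4. In the limitations paragraph of the Discussion, add participants' knowledge of their arm as a source of reporting bias, next to the two causes already given.

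The cost is wording in four places. No analysis, sample size or visit changes. The downside is that the stated blinding becomes less favourable. The change does not remove bias from the THI; it makes the claim match the protection that exists.
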